# Effectiveness of the serious game ‘You & I’ in changing mentalizing abilities of adults with mild to borderline intellectual disabilities: a parallel superiority randomized controlled trial

**DOI:** 10.1186/s13063-019-3608-9

**Published:** 2019-08-14

**Keywords:** Mentalization, Stress regulation, Intellectual disability, Serious game

## Abstract

**Background:**

Persons with mild to borderline intellectual disabilities generally show dysfunctions in mentalization and stress regulation, resulting in problematic social relationships and personal distress. Intervention programs may improve mentalizing abilities. The aim of this study is to examine the effectiveness of the serious game ‘You & I’ in changing mentalizing abilities and stress regulation in adults with mild to borderline intellectual disabilities.

**Methods:**

A two-arm, parallel, superiority randomized controlled trial will be used with 172 adults with mild to borderline intellectual disabilities. Participants will be randomly assigned to either the experimental group to play the serious game ‘You & I’ or a waitlist control group. Participants will be assessed at baseline, post intervention (5 weeks after baseline), and follow-up (6–8 weeks after post intervention). They also will fill in questionnaires for personal factors, personal development, personal well-being, social validity, autism spectrum quotient (demographic variables), mentalizing abilities (primary outcome measure), and stress regulation (secondary outcome measure).

**Discussion:**

The serious game ‘You & I’ aims to improve mentalizing abilities in adults with mild to borderline intellectual disabilities, which is expected to lead to improved regulation of stress in social relationships. The study’s unique feature is the use of a serious game to improve mentalizing abilities. If the intervention is effective, the serious game can be implemented on a broad scale in Dutch care organizations for people with intellectual disabilities as an effective preventive tool to improve mentalizing abilities.

**Trial registration:**

Netherlands Trial Register, NTR7418. Registered on 2 August 2018.

**Electronic supplementary material:**

The online version of this article (10.1186/s13063-019-3608-9) contains supplementary material, which is available to authorized users.

## Background

“Seeing oneself from the outside and others from the inside” [1]. This phrase is commonly used to describe mentalization, a concept that has been gaining attention since Fonagy reintroduced it in the early 1990s. Mentalization refers to “the mental process by which an individual implicitly and explicitly interprets the actions of himself or herself and others as meaningful on the basis of intentional mental states such as personal desires, needs, feelings, beliefs, and reasons” [2]. The capacity for mentalization is acquired in early childhood and is related to development in the domains of cognition, language, and social–emotional functioning [3]. Developmental delays in these domains in persons with mild to borderline intellectual disability (MBID) might be linked to limited capacity to mentalize [3]. It is important to examine whether interventions can help improve the mentalizing capacity of people with MBID.

Internal mental states drive how humans respond and act in certain situations. Mentalization involves recognition of mental states of the self and others, bringing beliefs, desires, intentions, goals, and emotions into awareness [4, 5]. Being aware of these mental states in the self and others facilitates coping, perceiving others as potential sources of support, and social alignment. Persons with MBID have a limited capacity to mentalize [3]. Predicting behavior of others and anticipating is therefore challenging [6–8]. Dysfunctions in mentalizing abilities may explain problems in social functioning among persons with MBID, such as destructive social interactions and social exploitation [9, 10]. Furthermore, because of limited social information processing as an executive function, people with MBID perceive more negative information, along with more difficulty remembering and processing information, limited working memory, and fewer problem-solving skills. The resulting stress makes learning mentalizing abilities more difficult [11, 12].

Within the construct of mentalization, three dimensions can be identified [13]. The first dimension is related to two modes of functioning, namely implicit and explicit functioning. Implicit mentalization refers to the unconscious, procedural, or automatic system of understanding others. Explicit mentalization involves a deliberate and conscious focus on mental content [14]. The second dimension is related to two objects, specifically the self and others. An individual can mentalize not only one’s own mental states but also the mental states of others; moreover, a person can mentalize one’s own relationships with other persons and, correspondingly, other persons’ relationships with one another [15]. The third dimension of the mentalization concept relates to its cognitive and affective aspects. Mental states in oneself and others can be cognitively focused as well as affectively laden to varying degrees [13].

According to Allen et al. [14] and Fonagy [16], humans first acquire the capacity for mentalization in the context of early attachment relationships. More specifically, the child develops mentalizing abilities within a secure attachment relationship, when the caregiver accurately and contingently mirrors the internal states of the child [13, 17]. The mirroring also needs to be *marked*. The caregiver contingently mirrors the internal state of the child [18]. This mirroring process enables the child to understand their own mental states and develop a stable sense of identity and, in turn, regulate their affect and distress [13, 18]. By also naming the mental state of the child, the child learns to recognize and name their mental state and those of others, which will improve their mentalizing abilities [19, 20].

Mentalization is not a static capacity but a dynamic, multifaceted ability whose development can be influenced by external factors such as stress [21, 22]. As Allen [15] points out: “Stress is the enemy of mentalization”. When high levels of stress are experienced, adequate mentalization becomes more difficult [23, 24]. To be more precise, the capacity to understand someone else’s mental states may be reduced, distorted, and less flexible when high levels of stress are experienced [22]. On the other hand, the ability to mentalize contributes to resilience against stress. In conclusion, support for mentalization may improve functioning even under circumstances that otherwise would have been experienced as stressful.

Awareness and understanding of mental states can be developed gradually by explicitly educating someone about mental states [25]. Empirical evidence suggests that mentalizing abilities can be improved with treatment programs such as mentalization-based therapy (MBT) [2]. In MBT, a therapist asks questions to strengthen the patient’s mentalizing abilities, such as ‘How do you think and feel about yourself and others?’, ‘Does this influence your behavior?’, ‘Can miscommunications in behavior and feelings lead to difficulties?’, and ‘How can you prevent and resolve those miscommunications?’ [16]. Randomized trials have shown that mentalization-based therapies improve interpersonal and social functioning [26, 27]. So far, treatment programs such as mentalization-based therapy have mainly focused on persons with personality disorders, while methods to stimulate the acquisition of mentalizing abilities for persons with MBID are still lacking. Moreover, current treatments for improving mentalizing abilities are time-consuming (treatment duration varying between 4 and 18 months), require supervision from qualified mental health professionals, and, consequently, are quite costly [28–30].

A promising and innovative method to improve mentalizing abilities of people with MBID is serious gaming. Serious games are computer applications that combine serious aspects, such as learning, with playful gaming elements [31]. Serious games have become increasingly popular over the years and results on their effectiveness are promising [32, 33]. Studies have also shown that serious games can be deployed successfully in the care for persons with intellectual disabilities when it comes to learning new skills and the development of abstract concepts [34]. Furthermore, MBT key elements can be realized in the serious game: a voice-over can, just like a therapist, instruct people with MBID indirectly (i.e. through interaction with an identifiable character) to recognize and name their mental state and those of others, which will improve their mentalizing abilities. Serious games can support learning which is particularly helpful for people with MBID, who learn by making abstract concepts concrete and receiving and processing new information step by step [3]. Moreover, serious games can be deployed at low cost and provide a unique learning environment wherein persons are allowed to practice new skills in a setting that is (un)likely to be realized in their daily lives [35, 36].

## Trial objective

The serious game ‘You & I’ (in Dutch: ‘Jij & Ik’) is a computer game developed with and for adults with MBID. The aim of the game is to improve mentalizing abilities, and stress regulation, focusing specifically on the three aforementioned dimensions of mentalization. In this study, the effectiveness of the serious game will be investigated, answering the following research questions: does the serious game ‘You & I’ improve mentalizing abilities in people with MBID; and does the serious game ‘You & I’ improve regulation of stress in adults with MBID?

## Hypotheses

The serious game ‘You & I’ is hypothesized to have a positive effect on mentalizing abilities, including the regulation of stress, in adults with MBID. The primary hypothesis is that being randomly assigned to the experimental group that plays the serious game will be associated with an improvement of the mentalizing abilities in adults with MBID as compared to being assigned to a waitlist control group. The secondary hypothesis is that being randomly assigned to the experimental group playing the serious game will be associated with an improvement of stress regulation in adults with MBID.

## Methods

Effectiveness will be examined using a parallel superiority randomized controlled trial (RCT) with a baseline, a post test after 4 weeks, and a follow-up assessment after 6–8 weeks (see Fig. 1). The RCT includes two groups: an experimental group who play the serious game ‘You & I’; and a control group who will be placed on a waitlist. The method of this study is reported according to the Standard Protocol Items: Recommendations for Interventional Trails (see Additional file 1).

**Fig. 1 Fig1:**
[figure not shown]
Flowchart of the study timeline

### Study population

A total of 172 adults with MBID, aged 18 years or older, will be recruited from the population of four Dutch care organizations that are specialized in disability care (Bartiméus, Ons Tweede Thuis, Cordaan, and ASVZ). Furthermore, the possibility to participate will be mentioned on websites (e.g. www.socialerelatiesenict.nl), on social media, and at various meetings. A diagnosis of MBID (IQ ranging between 50 and 85) needs to be reported, for instance, by the care organizations where the participant receives care. Inclusion criteria are having basic computer operation skills and having access to a computer with Internet connectivity. Adults need to give written consent for participation in the study and, if necessary, also their legal representative. Excluded from participation in the study are adults who are deaf and/or blind or adults who have serious mobility impairments for whom computer operation is not possible without aids.

### Sample size calculation

Linear mixed effect modeling with two conditions and three repeated measures will be conducted to analyze the effects on mentalizing abilities and stress regulation. The sample size is estimated based on previous studies measuring the mentalizing ability of perspective-taking using the Perspective Taking (PT) subscale of the Interpersonal Reactivity Index (IRI) and stress regulation using the Lifestress Inventory (LI) among people with intellectual disabilities. With the means used from both measures (for means, see [37, 38]), a desired power of 0.90, and α = 0.05, it is estimated that around 144 participants are needed, as calculated in GLIMMPSE [39]. Because there are three assessments, dropout of 20% will be taken into account. Thus, 172 participants will be recruited and randomized into two groups of approximately 86 participants in each group.

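### The allowance for 20% dropout is worked out as 144 × 1.2 rather than 144 / 0.8, so 172 recruited leaves about 138 completers, not the 144 required, and the calculation does not secure the 0.90 power

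*Protocol article*

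**What the plan says.** The Sample size calculation section of the protocol article gives its figures as a chain. With "a desired power of 0.90, and α = 0.05", "it is estimated that around 144 participants are needed". The dropout allowance follows, with the recruitment target presented as its consequence: "Because there are three assessments, dropout of 20% will be taken into account. Thus, 172 participants will be recruited", in two groups of about 86. The Methods paragraph of the Abstract repeats the target ("A two-arm, parallel, superiority randomized controlled trial will be used with 172 adults"), as does the Study population section. The article gives no other dropout rate and no other inflation rule. Both the Sample size calculation and the Data analysis sections plan a linear mixed-effects model over the three assessments.

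**The concern.** A dropout rate is a fraction of the people enrolled. An allowance for it has to leave the required number once that fraction is gone, so the requirement is divided by one minus the rate. The printed target looks as if 20% of the requirement was added instead. These two operations give different answers, and the one apparently used always gives too few.

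At stake is whether 172, the size at which the trial is presented, is consistent with the dropout and power printed beside it. There is also a practical side. A team that believes 172 covers 20% loss could lose up to 34 participants and think itself on plan, although the requirement of 144 is already missed once more than 28 are lost.

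**Working it through.** **Inputs, all from the Sample size calculation section:** requirement before dropout 144 (given as approximate); power 0.90; α = 0.05, sidedness not stated; dropout 20%; recruited 172, about 86 per group. The means, SDs and correlations behind the 144 are not printed, so 144 is taken as given.

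**1. Reproduce the printed figure.**
- Adding 20% of the requirement: 144 × 1.20 = 172.8. Rounded down to an even total this is 172, or 86 per arm, which is the printed figure.
- Dividing by the retained fraction: 144 / 0.80 = 180, or 90 per arm. This is 8 more than printed (8 / 172 = 4.7%).

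**2. Could the approximate 144 explain the gap?** With 143, division gives 143 / 0.80 = 178.75; with 145 it gives 181.25. For 172 to be right under division, the requirement would have to be 172 × 0.80 = 137.6. Rounding of 144 does not explain the difference.

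**3. What 172 delivers.**
- Completers after 20% loss: 172 × 0.80 = 137.6, that is 137 or 138, so 6 to 7 below 144.
- People added: 172 − 144 = 28. People lost at 20%: 172 × 0.20 = 34.4.
- Largest dropout that still leaves 144: 1 − 144 / 172 = 0.163, or 16.3%.

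**4. Power if dropouts contribute nothing.** Scaling from 0.90 at N = 144 with the normal approximation, two-sided α assumed:

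power(N) = Φ[(1.960 + 1.2816) × √(N / 144) − 1.960]

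- N = 137.6: 3.2416 × √0.9556 − 1.960 = 3.2416 × 0.9775 − 1.960 = 1.209, and Φ(1.209) = 0.887.
- N = 172 (nothing lost): 3.2416 × √1.1944 − 1.960 = 1.583, and Φ(1.583) = 0.943.

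The result changes little with the form of the test:

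| Approximation | N = 137 | N = 138 | N = 172 |
|---|---|---|---|
| Normal, two-sided | 0.885 | 0.887 | 0.943 |
| Normal, one-sided | 0.887 | 0.889 | 0.940 |
| Noncentral t, two-sided | 0.885 | 0.887 | 0.944 |
| Noncentral F, 2 df | 0.884 | 0.886 | 0.946 |

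The 2-df row is included because a Group × Time effect over three assessments has 2 degrees of freedom. The completers-only loss against 0.90 is 1.1 to 1.6 percentage points.

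**The case against.** The strongest objection concerns power. A reader might infer from the shortfall that the trial will not reach 0.90. The article does not support that. Randomization follows the baseline assessment, so every randomized dropout has baseline data, and those who leave after the post-intervention assessment have that as well. A likelihood-based mixed model can use those records. Nothing in the article restricts the analysis to completers, and the partial intention-to-treat analysis named under Data analysis is not defined. Power therefore lies between about 0.885 (dropouts contribute nothing) and about 0.94 (no information lost), and that range includes 0.90. This part of the objection stands.

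It does not rescue the arithmetic. The section adds participants for dropout and derives 172 from that step, so by its own logic the addition should restore 144. If partial data were the reason for a smaller allowance, the article would have to say so, and it does not. Someone lost before the post-intervention assessment also adds little to a Group × Time contrast.

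Two further objections carry some weight. The article calls both the 144 and the 86 per group approximate, and it never states that 144 completers will remain. It also shows no inflation formula, so the factor of 1.2 is inferred. The inference is close, however, since 172.8 sits next to the printed 172, and step 2 shows that rounding does not close a gap of 8. Nor is this a matter of condensation in a journal article: all three numbers are printed, and they disagree.

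**Conclusion.** The point holds as an arithmetic inconsistency of small effect. At the stated 20% dropout, 172 recruited leaves about 138 completers, 6 to 7 below the protocol's own requirement, and 144 is retained only up to 16.3% dropout. This follows from the printed figures alone and is certain.

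The consequence for power is limited and less certain. The calculation does not secure 0.90. A completers-only lower bound is about 0.885 to 0.89, and the mixed model may recover the rest. That bound assumes that 144 does give 0.90, that power scales with the number analysed, that loss is similar in the two arms, and (for the main figure) that α is two-sided. The 144 itself cannot be checked from the article. The validity of the trial is not in question, but a printed sample size should agree with the dropout it claims to cover.

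**What to change.** Add or replace one sentence in the Sample size calculation section. Either of these is consistent with keeping 172:

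- State that recruiting 172 retains the required 144 up to about 16% dropout.
- State that 20% dropout from 172 leaves about 138 completers, for which a completers-only lower bound on power is about 0.89, and that the mixed model is expected to use the partial data of those who leave. The 0.89 must be labelled as a bound with its assumptions, not printed as the power of the planned analysis.

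If the sponsor wants 144 completers at 20% dropout to stand, the consistent target is 180 (90 per arm), and 172 must then be changed in the Abstract and in the Study population section too.

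The restatement costs one sentence and changes nothing in the conduct of the trial. The larger target costs 8 more participants.

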### Study procedure and randomization

Individuals who sign up for the research both via the care organization as well as via the Internet or any other route and who meet the inclusion criteria will receive an information brochure. Persons who want to participate in the study are asked to sign the consent form and return it to the researcher. In case of legal incapacitation, the legal representative of the participant is asked to sign and return a consent form on behalf of the participant.

Data collection for each participant takes 12–14 weeks. Participants will be assessed at baseline (T0), post intervention (T1, 5 weeks after baseline), and follow up (T2, 6–8 weeks after T1). During all three assessments, participants fill out a set of digital questionnaires (for all measurements, see Measures). A software program (e.g. Qualtrics or Survalyzer) will be used to gather data through the digital questionnaires. Completing the questionnaires will take up to 90 min per assessment. During all assessments, an independent researcher is present to assist the participants with completing the questionnaire at home or in their care home. The researchers will follow a standard protocol on how to assist the participants.

After informed consent and baseline assessment, blind for intervention, participants will be individually randomized into two groups using stratified randomization in combination with block randomization with varying block sizes of 4 and 6. To balance contextual factors, randomization will be stratified with regard to care organization. An independent researcher will produce the allocation schedule using a computerized random number generator and afterward conceal the schedule for the researchers. Blinding is only possible for the baseline assessment and, after that, both participants and the researchers will know to which group participants have been assigned.

After randomization, participants within the experimental group will be offered the serious game ‘You & I’, while participants within the control group will be placed on a waitlist. Participants from the experimental group will be asked to play the serious game on their own computer device at home or on a computer device of their care home. They have to complete eight gaming levels within 4 weeks, playing the game twice a week. To remind the participants to play the game, they will receive an impersonal email or text message on their phone twice a week asking them whether they have already played the game. Anonymous digital game statistics will measure the compliance of the participants (how often the computer game has been completed). After 4 weeks, the post-intervention assessment is administered, and 6–8 weeks later the participants complete the follow-up assessment. Participants from the control group can play the serious game after they have completed the follow-up assessment.

5	Explicit functioning	Cognitions, affections, the self, and others
6	Implicit functioning	Cognitions, affections, the self, and others
7	Booster level	Cognitions, affections, the self, others, and implicit and explicit functioning
8	Booster level	Cognitions, affections, the self, others, and implicit and explicit functioning

## Measures

All data will be collected through computerized assessments at baseline, post intervention, and follow-up assessment. Participants can fill out the digital questionnaires at home or in their care home. When needed, participants will receive support from an independent researcher, who will be present during all assessments and who will follow a standard protocol on how to assist the participants. Figure 2 provides an overview of the measures and time of assessment.

**Fig. 2 Fig2:**
[figure not shown]
Schedule of enrollment, allocation, intervention, and assessments

### Demographic variables

#### Minimal dataset (MDS; T0)

To measure demographic variables, the minimal dataset (MDS) ‘Basic MDS’ and ‘Basic MDS for adults with an intellectual disability’ will be used, including the Personal Wellbeing Index—Intellectual Disability (PWI-ID) [41, 42]. The MDS is a set of questions on demographic variables for everyone who collects data of persons with intellectual disabilities. The MDS focuses on questions in the following domains: personal factors, personal development, and personal well-being. The questionnaire consists of 32 items, measuring, for example, gender, age, and intellectual functioning.

